### 3.9 Potential Risks

We do not anticipate any major safety concerns with the use of BLT. All BLT lamps will be cleaned and sterilized before being given to participants, as well as when participants leave the hospital, to prevent possible spread of infection and reduce contamination concerns. The side effects that have been reported with BLT include headache, eyestrain, irritability/agitation, mania associated with bipolar disorder, and blurred vision or nausea, but are typically mild and disappear after the first few days. Participants have rarely dropped out of studies due to BLT side effects.

### 3.10 Potential Benefits

Light therapy was first introduced in 1984 as a treatment for Seasonal Affective Disorder. It has proven to be quite effective at reducing depression in this population. More recently, BLT has been marketed and studied for all types of depression, as well as for mood, energy, fatigue, alertness, focus, and concentration. BLT has been shown to reduce depressive symptoms in patients with seasonal depression as well as non-seasonal depression or depressive symptoms. Some studies have also found BLT to improve anxiety, sleepiness, fatigue, sleep efficiency, and health-related quality of life.

## 4. TRIAL DESIGN

### 4.1 Summary of Trial Design

We will conduct a RCT with a treatment period of 4 weeks and 12 week follow-up post-cardiac surgery. A total of 38 cardiac surgery participants will be randomized 1:1 to one of two treatment arms: 1) BLT or 2) Dim light (control group). Participants randomized to the BLT arm will receive a lamp emitting 10,000 lux light intensity, while those in the dim light arm will receive lamps emitting 500 lux. These lamps will both appear bright to participants, but only the high intensity light has been shown to be therapeutic. We will be using the TRAVelite Desk Lamp manufactured by Northern Light Technologies. Study personnel and participants will be blinded as to treatment allocation. Permutated block randomization will help ensure a balance of known and unknown confounders. Informed consent will be obtained in person from all individuals. Potential participants will be informed that the purpose of this pilot study is to assess the feasibility of carrying out a large trial to investigate BLT for depressive symptoms in cardiac surgery patients. The follow-up visits and data to be collected will be discussed, as well as alternatives to participation, issues of confidentiality, and

participants' rights and responsibilities. Potential participants will be given sufficient time to ask questions and decide whether or not to participate prior to signing and receiving a copy of the signed consent form.

Participants will also be provided with an information sheet containing study procedures and contact information for study personnel. Participants in both groups will begin using the lamps in-hospital and will continue the treatment at home for the remainder of the 4 weeks post-surgery. At baseline, participants will complete the Patient Health Questionnaire 9 (PHQ-9), Depression Anxiety Stress Scale short version (DASS-21), and Short Form (36) Health Survey (SF-36) questionnaire in order to determine index levels of depressive symptomology (PHQ-9, DASS-21) and health-related quality of life (SF-36). A case report form, to collect demographic and clinical information, will be completed at baseline. On day 4 and on the day of discharge, participants will complete questionnaires and a CRF will be completed assessing adherence, tolerability, and side effects. There will be a clinic visit at week 4, when patients will return their lamp and complete questionnaires, and study personnel will complete a case report form to monitor treatment adherence. At week 12, participants will have the option to complete their questionnaires online or by mail. To compensate participants for expenses incurred due to participation (parking, childcare, opportunity costs, etc.), they will receive \$25 at week 4 and a \$20 prepaid VISA card after completing the questionnaires at week 12.

#### 4.2 Schematic Diagram of Trial Design

[figure not shown]

#### 4.3 Primary Endpoint

(1) Recruitment rate

4.4 Secondary Endpoints

(2) Retention rate: percentage of participants who remain in the study at week 12.

(3) Adherence rate: percentage of participants that used their lamp on  $\geq 60\%$  of mornings within an hour of waking for at least 25 minutes.

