| 3.3 | Route of Administration                 | 
Participants will be exposed to the light by sitting 12 inches from the lamp while looking at a surface that the light is reflecting onto. They should not look directly into the light, but may glance at it occasionally. This therapy can be done while reading, eating, or doing other seated activities.
                                                                                                                                                                                                                                                                                                                                                                                                                                                                                                                                                                                                                                                                                                  |
| 3.4 | Dose and Dosage Regimen                 | 
Participants will be instructed to use the light for 30 minutes each morning within an hour of waking, but not past 1:00 pm (to ensure that sleep does not become disturbed). The light must be approximately 12 inches from the participants' faces. Rulers will be used in hospital to ensure participants use the lamp at the proper distance. The length of time, and distance from the lamp both affect the intensity of light being received. Participants' eyes should be open when using the lamp, but they should not look directly into the lamp.
                                                                                                                                                                                                                                                                                                                                                                                                                                                    |

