#### 5.3.2 Treatment

Participants in the 10,000 lux lamp group will be supplied with an electric BLT lamp emitting 10,000 lux light intensity. Participants in the 500 lux lamp group will be instructed to use the lamp for 30 minutes each morning, preferably upon waking, but not past 1:00 pm. Use will be monitored via self-

report at the day 4, day of discharge, and week 4 visits.

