##### 5.4.2 Data Collection

A case report form (CRF) will be completed at baseline, day 4, day of discharge, and week 4. At week 12, participants will complete a survey to provide additional data. At baseline, the CRF will collect demographic and clinical information, including medical history, current medications, surgery details, and depression history. Participants will also complete three questionnaires: SF-36, PHQ-9, and DASS-21. At day 4, day of discharge, and week 4, participants will be asked about protocol adherence, symptoms, and AEs or SAEs. They will also complete the same three questionnaires to assess depressive symptoms and health-related quality of life. At week 12, participants will be asked to complete these same questionnaires as well as a survey assessing symptoms via distance either through mail or an online questionnaire website. During enrollment, participants will be asked about their preference (i.e. mail or online). If they choose the mail option, the questionnaires will be mailed to their address, along with a return envelope and stamp. If they choose the online option, they will be sent an email at week 12. The email will contain a link to the online survey (SurveyMonkey), which they can use to access the survey and complete the questionnaire.

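### The adherence endpoint is defined morning by morning, but use is collected only by self-report at three visits, and the protocol gives two different timing instructions

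*Protocol*

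**What the plan says.** **Definition.** Section 4.4 makes the adherence rate a secondary endpoint: the share of participants who used the lamp on at least 60% "of mornings within an hour of waking for at least 25 minutes". A morning qualifies only if three things hold: the lamp was used, the use fell within the hour after waking, and it lasted long enough.

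**Measurement.** Section 5.3.2 has use monitored by self-report, taken as a "report at the day 4, day of discharge, and week 4 visits". Section 5.4.2 adds: "At day 4, day of discharge, and week 4, participants will be asked about protocol adherence, symptoms, and AEs or SAEs". Section 4.1 says that a case report form covering adherence is completed at these visits, and that the lamp comes back at week 4. No diary, usage log or lamp timer is described. Section 5.4.4 gives the week 4 visit a window of 7 days either side and shows no case report form at week 12.

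**Timing instruction.** Section 3.4 tells participants in general to "use the light for 30 minutes each morning within an hour of waking, but not past 1:00 pm". In section 5.3.2 the 500 lux group is "instructed to use the lamp for 30 minutes each morning, preferably upon waking, but not past 1:00 pm". That sentence has no one-hour limit, and 5.3.2 gives no matching instruction for the 10,000 lux group.

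**Role of the endpoint.** Adherence is named in the primary objective (1.2), and 7.3 says that it has to be assessed before a full trial is run.

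**The concern.** The definition needs, for each morning, a wake time, a start time and a duration. The plan as written asks about these at three visits, two of them in hospital. After discharge there is one further adherence contact, at week 4, and the participant must then summarise several weeks against a three-part rule. An analysis plan cannot repair this later, because it cannot recover per-morning data that were never recorded.

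The two timing instructions are a second, separate problem. A participant can do what 5.3.2 asks and still fail the endpoint. If the sections are applied literally, the arms are instructed differently but scored by one rule.

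At stake is one of the quantities the pilot exists to deliver. A rate that partly reflects recall and wording is a weaker basis for deciding on a full trial.

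**Working it through.** **1. The plan's own adherence figure.** Section 7.3 gives a 95% confidence interval of +/- 8% for a compliance rate of 80% with 38 participants. The usual half-width is 1.96 × √(0.80 × 0.20 / 38) = 1.96 × 0.0649 = 0.127, or 12.7 points, so the figure does not reproduce. That is a separate matter from this point. What counts here is that such an interval covers sampling error only and makes no allowance for misclassified participants.

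**2. The cut-off in mornings.** Treatment lasts 4 weeks (3.6), nominally 28 mornings. 0.60 × 28 = 16.8, so 17 qualifying mornings are needed (17/28 = 60.7%; 16/28 = 57.1% fails). The 28 is nominal because 3.6 starts the period at randomization and 5.3.1 starts it after surgery.

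**3. Share of mornings resting on the week 4 report.** The protocol does not give the day of discharge, so this is an assumption shown as a range:
- discharge on day 5: (28 − 5)/28 = 82%
- discharge on day 7: (28 − 7)/28 = 75%
- discharge as late as day 14: (28 − 14)/28 = 50%

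**4. Sensitivity near the cut-off.** Assume each participant has the same chance q of a qualifying morning, independently across 28 mornings. The adherent share is P(X ≥ 17) with X ~ Binomial(28, q):

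| q | Adherent share |
|---|---|
| 0.40 | 2.2% |
| 0.50 | 17% |
| 0.55 | 34% |
| 0.60 | 55% |
| 0.65 | 75% |
| 0.70 | 90% |
| 0.80 | 99.5% |

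A reporting shift from 0.55 to 0.65, about 0.10 × 28 = 2.8 mornings per participant, moves the rate from 34% to 75%. Far from the cut-off the rate barely moves. Real participants differ from one another, which would flatten this curve, so the table shows where the risk lies and is not a forecast.

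**5. Direction of the error.** Observed rate = t × sens + (1 − t) × (1 − spec), where t is the true adherent share. With t = 60% and error rates assumed (the protocol gives none):
- sens 1, spec 0.90: 0.60 + 0.40 × 0.10 = 64%
- sens 1, spec 0.75: 0.60 + 0.40 × 0.25 = 70%
- sens 1, spec 0.50: 0.60 + 0.40 × 0.50 = 80%
- sens 0.90, spec 0.90: 0.54 + 0.40 × 0.10 = 58%

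One-sided over-reporting raises the rate; symmetric error can lower it.

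**6. The timing conflict.** Section 3.4 reads "30 minutes each morning within an hour of waking, but not past 1:00 pm"; section 5.3.2 reads "for 30 minutes each morning, preferably upon waking, but not past 1:00 pm". Take a participant who uses the lamp for the full 30 minutes on all 28 mornings, always before the afternoon limit, but starts more than an hour after waking on 12 of them. Under 5.3.2 every morning complies. Under 4.4 only 28 − 12 = 16 qualify, and 16/28 = 57.1% is non-adherent. This mechanism lowers the measured rate.

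**The case against.** The strongest reply is that visit-based self-report is a reasonable choice for a pilot of 38 people, one of whose stated aims is to find out which data values were missed (4.5). The endpoint is a coarse cut, so exact daily times do not matter for participants well above or below it. The case report form items are not shown and could include a log or a question on mornings per week. A daily card is still self-report, can be filled in afterwards, and may itself prompt use. Section 3.4 already gives one instruction for everyone, and 5.3.2 reads like a drafting slip, with supply described for one arm and use for the other.

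Much of this stands. It confines the risk to participants near the cut-off, and a daily record cannot be excluded, although none is described. It does not explain how a three-part morning rule is to be scored from one report covering the home period, and a drafting slip in an instruction that feeds an endpoint still needs correcting.

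A reader might go further and infer two things that the protocol does not support:
- **That the rate will come out too high.** The protocol has no data on self-report error, and the timing conflict acts in the opposite direction.
- **That participants who miss week 4 are left out and so inflate the rate.** No such rule is stated. Section 4.4 speaks of participants without restriction, and 5.4.6 retains data collected up to withdrawal. The loss-to-follow-up flow chart in 5.4.5 is not shown and may provide for a missed visit. The denominator may properly be set in an analysis plan. Section 5.4.5 also ties week 4 to the post-operative appointment to support attendance.

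**Conclusion.** The point holds in two parts.

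First, the endpoint is defined per morning, while the measurement described is retrospective self-report at three visits, with everything after discharge resting on the last of them. The rate is therefore at risk of misclassification near the cut-off of 17 of a nominal 28 mornings, in a direction that cannot be determined. The share of mornings affected is 75% to 82% if discharge falls on day 5 to 7. How far the rate could move depends on how many participants lie near the cut-off, which is unknown; the 34% to 75% swing rests on a common, independent per-morning probability.

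Second, 3.4 and 5.3.2 differ on timing, and the endpoint scores the version in 3.4, so a participant who follows 5.3.2 can be counted as non-adherent. This part rests on the text alone and needs no assumption.

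Both should be corrected. Neither undermines the randomization or the primary endpoint, the recruitment rate.

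**What to change.** 1. Issue a one-page daily card with each lamp, with columns for wake time, lamp on and lamp off. Collect it with the lamp at week 4 and state in 4.4 and 5.4.2 that the adherence endpoint is derived from it. If the case report form already holds a daily record, say so in 5.3.2 instead.
2. Reconcile 3.4, 5.3.2 and 4.4 so that both arms have one timing instruction, stated for both, and the endpoint scores that instruction. Which instruction to adopt is for the investigators.

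Cost: a printed card and about a minute a day for the participant, with no added visit. Some cards will be incomplete or filled in afterwards. The card may also prompt use, so the measured adherence would be adherence with a card; a full trial should either keep the card or allow for the difference. The second change is to wording only.

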#### 4.5 Tertiary Endpoints

- (4) Determination of process time required
- (5) Identification of unforeseen challenges
- (6) Identification of important data values that were not measured

#### 4.6 Measures Taken to Reduce Bias

##### 4.6.1 Randomization

The use of randomization should result in a balance of known and unknown confounders. We will use stratified, permuted block randomization. A permuted block design will prevent study personnel from identifying the randomization sequence.

##### 4.6.2 Blinding

Randomization to the therapy lamps will be blinded as to whether they emit 10,000 lux or 500 lux. The lamps are identical in appearance when turned off. To prevent study personnel unblinding, participants will be asked to turn on their lamp after the study personnel leave the room. All packaging and labeling of the lamps will be performed by non-study personnel. Lamps will be assigned using a unique blind code which will be issued for each participant at the time of randomization. This ensures all individuals at the study centre remain blinded.

##### 4.7 Study Population

Participants will be recruited from post-cardiac surgery patients experiencing moderate to severe depressive symptoms.

#### 4.8 Inclusion and Exclusion Criteria

##### 4.8.1 Inclusion Criteria

- 1) Undergoing cardiac surgery;
- 2) Age  $\geq 18$  years;
- 3) Score of  $\geq 8$  on the PHQ-9;
- 4) Able to understand and to provide informed consent in English or French; and
- 5) Likely to be available for follow-up.

##### 4.8.2 Exclusion Criteria

- 1) Pregnant or lactating females;
- 2) Medical condition with a prognosis  $< 12$  weeks;
- 3) History of bipolar disorder, SAD, psychosis, or dementia;
- 4) Medical condition contraindicating use of BLT (ocular or retinal pathology: glaucoma, cataracts, retinal detachment, retinopathy, diabetes);
- 5) Medical condition that increases photosensitivity (e.g. systemic lupus erythematosus,

- rosacea, psoriasis, albinism);
- (6) Current use of medication that increases photosensitivity (e.g. St John's Wort, lithium, melatonin, tetracycline, Accutane, Benzoyl peroxide, Retin-A);
- (7) Less than one month following previous BLT;
- (8) Light induced epilepsy or migraines; or
- (9) Suicidal ideation.

## 5. TRIAL PROCEDURES

This study will be conducted according to ethical principles stated in the Declaration of Helsinki, and the consent forms will take into consideration the well-being, free-will and respect of the participants, including respect of privacy.

### 5.1 Recruitment

Participants will be recruited using recruitment flyers in the Cardiac Care Unit (CCU) and the cardiac surgery waiting room. Initial contact will be accomplished in person by the study coordinator prior to surgery. Interested potential participants will be asked to provide informed consent and confirm eligibility.

### 5.2 Enrollment

Informed consent will be obtained in person from all individuals. Potential participants will be given sufficient time to ask questions and decide whether or not to participate prior to signing and receiving a copy of the signed consent form. Study personnel will complete an inclusion and exclusion form to confirm eligibility based on the criteria listed above. As part of the screening process, potential participants will complete the PHQ-9 questionnaire to determine whether they are currently experiencing depressive symptoms. A cut off score of 8 will be used (sensitivity: 0.82; specificity: 0.83). Potential participants who do not sign the consent form or who do not meet the eligibility criteria will be considered screen failures and will not be randomized to a treatment group.

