### 7.3 Sample Size Justification

The sample size of 38 participants (19 per arm) was chosen in order to appropriately test the study procedure and methods within the available timeframe. Acceptability and adherence to the intervention must be assessed before conducting a full trial. A sample size of 19 participants per arm should be able to demonstrate the ability to execute the specific protocol. If 100 eligible patients are identified, we will be able to estimate a participation rate of 38% to within a 95% Confidence Interval (CI) of +/- 7%. Additionally, with a sample size of 38, we will be able to estimate a compliance rate of 80% to within a 95% CI of +/- 8%.

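### The participation rate among eligible patients planned in Section 7.3 is not identified if, as the protocol most naturally reads, the PHQ-9 is completed only after consent

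*Protocol*

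**What the plan says.** Protocol Section 4.3 lists one primary endpoint, "Recruitment rate", without numerator, denominator or time unit. The two secondary rates in 4.4 are both defined.

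Section 7.3 supplies the only denominator: "If 100 eligible patients are identified, we will be able to estimate a participation rate of 38" per cent, "to within a 95% Confidence Interval (CI) of +/- 7" per cent. It calls this a participation rate. The trial size in the same section is 38, or 19 per arm.

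Inclusion criterion 3 in Section 4.8.1 requires a PHQ-9 score of 8 or more. Four sections bear on when that score is obtained:

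- Section 5.1: "Interested potential participants will be asked to provide informed consent and confirm eligibility".
- Section 5.2 describes consent, then the inclusion and exclusion form, then the PHQ-9 as part of screening. It ends: "Potential participants who do not sign the consent form or who do not meet the eligibility criteria will be considered screen failures".
- Section 3.6 lists consent, a finding of eligibility and randomisation, in that order, as what precedes treatment.
- Section 5.4.1 names eligibility before consent, but says only that participation starts once both are in place.

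No section provides for a PHQ-9, or any other eligibility assessment, in people who decline, or for a count of eligible non-participants.

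**The concern.** A participation rate among eligible patients needs a count of everyone eligible, including those who refuse. If the PHQ-9 follows consent, the eligibility of refusers is never established. The numerator is then known, but an essential part of the denominator is not.

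The pilot exists to judge whether a full trial is feasible. A low yield may come from patients declining or from few patients scoring 8 or more, and the two call for different remedies. A rate whose denominator cannot be counted does not separate them. The missing scores cannot be recovered once recruitment has ended.

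**Working it through.** **Inputs from the protocol.** 38 randomised (7.3); 100 eligible patients and a 38% participation rate (7.3); stated 95% half-width of 7 points (7.3); PHQ-9 cut-off of 8, sensitivity 0.82, specificity 0.83 (5.2); depression in at least 15-20% of cardiac surgery patients (1.3).

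**Assumptions, not in the protocol.** R, the number of refusers; q, the share of refusers who would have met all criteria, including PHQ-9 of 8 or more.

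**Step 1: the plan's own precision figure.** The 95% half-width is 1.96 × √(p(1−p)/n) = 1.96 × √(0.38 × 0.62/100) = 1.96 × 0.0485 = 9.5 points. The Wilson interval is 29.1% to 47.8% and the Clopper-Pearson interval 28.5% to 48.3%. The stated 7 points is not reproduced. It corresponds to about 85% confidence, or to about 1.96² × 0.2356/0.07² = 185 eligible patients. A finite-population factor of √0.62 would give 7.5 points, but the protocol offers no basis for one. This is a separate error; the identification problem below does not depend on it.

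**Step 2: what the described flow observes.** Eligible patients = 38 + R × q, so participation = 38/(38 + R × q). R can be counted. Without a PHQ-9 on refusers, q cannot.

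With R = 62, the number that makes 38 participants 38 of 100 when every refuser is eligible:

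| q | Eligible patients | Participation |
|---|---|---|
| 1.00 | 38 + 62.0 = 100.0 | 38% |
| 0.50 | 38 + 31.0 = 69.0 | 55% |
| 0.20 | 38 + 12.4 = 50.4 | 75% |
| 0.15 | 38 + 9.3 = 47.3 | 80% |

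The result does not depend on R = 62. With R = 150, the rate runs from 38/188 = 20% (q = 1) to 38/60.5 = 63% (q = 0.15). With R = 300, it runs from 38/338 = 11% to 38/83 = 46%.

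**Step 3: how far the denominator matters (illustration only).** The share scoring 8 or more is 0.82 × prevalence + 0.17 × (1 − prevalence): 0.2675 at 15% and 0.300 at 20%. Then 38 randomised need about 38/0.300 = 127 to 38/0.2675 = 142 consented screens, before other exclusions. If 38% of those approached consent (an assumption), about 333 to 374 are approached. The same 38 people are then 10-11% of those approached, 27-30% of those screened, and about 100% of those actually found eligible. If consent is anywhere from 20% to 70%, about 181 to 710 are approached and the overall rate is about 5% to 21%.

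**The case against.** **The endpoint can still be measured.** A reader might infer that the primary endpoint cannot be measured at all. The protocol does not support that. Section 4.3 leaves the recruitment rate undefined, Section 7.3 speaks of a participation rate in a conditional precision illustration, and a rate per patient approached or per month is obtainable from the planned procedures. This stands. The problem is confined to the eligible-patient rate, the only form for which the protocol gives a denominator.

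**The order is inferred.** Section 5.2 has potential participants complete the PHQ-9 and does not expressly limit it to signers. Section 5.1 joins consent and eligibility without stating a sequence, and 5.4.1 names eligibility first. This stands in part: consent first is the most natural reading of 3.6, 5.1 and 5.2 together, but it is not stated outright. If the PHQ-9 was meant to come first, the text needs to say so.

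**The shared label loses nothing.** A reader might infer that calling refusers and ineligibles alike screen failures destroys the split between them. It does not: the consent form and the inclusion and exclusion form already allow the two to be told apart. What those forms cannot supply is a refuser's PHQ-9 score.

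**The analysis plan may define the rate.** A SAP not shown here may well choose a denominator. It cannot create scores that the protocol's procedures do not collect.

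**The stakes are limited.** This is a 38-patient pilot with descriptive analysis and no stated go/no-go threshold. That is fair, and it limits the consequence to how the feasibility result can be interpreted.

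**Conclusion.** The point holds in limited form. On the most natural reading of the protocol, the participation rate among eligible patients set out in Section 7.3 is not identified, because the eligibility of those who decline is not observed. With 38 randomised and an assumed 62 refusers, the same data fit any rate from 38% (all refusers eligible) to 80% (15% eligible). That 42-point range compares with a sampling half-width of about 9.5 points when all 100 are truly known to be eligible. Dividing instead by the patients actually found eligible would give close to 100% whatever the uptake, though the protocol does not say it will do this.

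The conclusion rests on consent preceding the PHQ-9. The size rests on assumed values of R and q, which the protocol does not give. The 10-11%, 27-30% and 100% figures only illustrate how much the choice of denominator matters. They rest on an assumed consent rate and do not measure an error in the plan.

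**What to change.** 1. In 4.3 and 7.3, define the primary endpoint on denominators that can be counted: overall recruitment = randomised / approached, and randomised per month of open recruitment. Break it down into consent rate = consented / approached and eligibility yield = eligible / PHQ-9 screened. Define approached as contacted in person by the study coordinator (5.1), so that people who are not interested are counted.
2. In 5.2, report declined consent separately from consented but ineligible, with the criterion failed. The existing forms already allow this.
3. Recompute the precision statement in 7.3 for the chosen denominator. If 38 of 100 is kept as an example, the 95% half-width is about 9.5 points.
4. If a PHQ-9 before consent was intended, state that order explicitly in 3.6, 5.1 and 5.2 instead, with ethics approval for the pre-screen. The eligible-patient denominator can then stay.

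Cost: protocol wording and one extra column on the screening log, with no extra visits. The downside of items 1 to 3 is that participation among eligible patients is no longer the headline figure.
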